## Abstract

**Background:**

Depression and binge drinking behaviours are common clinical problems, which cause substantial functional, economic and health impacts. These conditions peak in young adulthood, and commonly co-occur. Comorbid depression and binge drinking are undertreated in young people, who are reluctant to seek help via traditional pathways to care. The iTreAD project (internet Treatment for Alcohol and Depression) aims to provide and evaluate internet-delivered monitoring and treatment programs for young people with depression and binge drinking concerns.

**Methods:**

Three hundred sixty nine participants will be recruited to the trial, and will be aged 18–30 years will be eligible for the study if they report current symptoms of depression (score 5 or more on the depression subscale of the Depression Anxiety Stress Scale) and concurrent binge drinking practices (5 or more standard drinks at least twice in the prior month). Following screening and online baseline assessment, participants are randomised to: (a) online monthly self-assessments, (b) online monthly self-assessments + 12-months of access to a 4 week online automated cognitive behaviour therapy program for binge drinking and depression (DEAL); or (c) online monthly assessment + DEAL + 12-months of access to a social networking site (Breathing Space). Independent, blind follow-up assessments occur at 26, 39, 52 and 64-weeks post-baseline.

**Discussion:**

The iTreAD project is the first randomised controlled trial combining online cognitive behaviour therapy, social networking and online monitoring for young people reporting concerns with depression and binge drinking. These treatments represent low-cost, wide-reach youth-appropriate treatment, which will have significantly public health implications for service design, delivery and health policy for this important age group.

**Trial registration:**

Australian and New Zealand Clinical Trials Registry ACTRN12614000310662. Date registered 24 March 2014.

## Background

Adolescence and young adulthood represents a critical period of development in which health and social behaviours are established. During this time, young people acquire a wide range of skills and behaviours via their family, social and community environments, and these influences will affect their physical, psychological and social health throughout their lives [1]. Early drinking during this period poses a risk later in life, with binge drinking during adolescence and young adulthood being associated with a 40–60 % increase in likelihood of developing alcohol dependence, regardless of family history [13]. Prevalence rates for alcohol use disorders in Australia are some of the highest worldwide [2]. Incidence rates for depression are much higher among young people than in any other age group [1], and at least 50 % of young people who experience a depressive episode will experience one or more recurrent episodes of depression [3].

Young people drink differently from adults. In Australia and the USA, 90 % of alcohol consumption in young people occurs in the form of binge drinking 5 or more standard drinks in one sitting, [4]. Epidemiological data indicate that binge drinking peaks at age 19, with the aim of getting drunk as quickly and cheaply as possible, in part to cope with a range of emotional issues present at that age [5]. Binge drinking in young people crosses all socioeconomic domains, and exerts its impact across all demographics and communities.

Mental disorders, particularly depression, will generally emerge during adolescence and young adulthood, and remain a significant challenge for our young people. Australian data indicate that 1 in 4 people aged 16–24 years will experience a mental health disorder in a 12 month period, and up to 43 % report feeling sad for at least 2 weeks in the past year [5]. Incidence rates for depression are much higher among young people than in any other age group, and at least 50 % of young people who experience a depressive episode will experience one or more recurrent episodes of depression [5].

Depression and binge drinking represent a lethal combination for young people, as evidenced by higher rates of land transport accidents and intentional self-harm than in any other age group 2 in every 5 deaths, [1]. Binge drinking is a common correlate of road accidents, and after a previous suicide attempt, depression is the next highest risk factor for youth suicide [1]. Heavy alcohol use, including binge drinking, plays a role in both the development and progression of mental disorders, particularly depression [6].

### Treatment access and retention of young people in traditional treatments is poor

There is hope of full functional, physical and psychological recovery from the consequences of depression and binge drinking. Animal models have shown that, with abstinence from a period of heavy binge drinking, neural stem-cell development can be re-instated, along with the formation of new neurons and other brain cells indicative of brain growth [7]. Effective treatment of depression during early days of abstinence from binge drinking can prevent the development of a depressive episode, and in young mice has been shown to better restore the ability of the brain to produce new cells [8].

In humans, psychological interventions, which allow the exploration of links between disorders, are of likely benefit to people with comorbid conditions, and are worthy of closer development and testing, in light of the potential for interactions between alcohol use and pharmacotherapy [9]. Psychological treatment is often preferred over pharmacotherapy [10], especially among young people [11]. Good interpersonal relationships and social connectedness have also been shown to exert a significant protective effect on the development of depression and in depressive and alcohol relapse [3, 12].

Despite this, treatment access for young people remains a critical challenge for traditional mental health and drug and alcohol services [13]. Patients under 25 years accounted for the least number of encounters with a general practitioner 2008–9 in Australia (20 %), representing a decrease in the frequency with which this age group is accessing primary care services since 1999–00 [1]. Only 2 % of 15–24 year olds accessed a psychologist in 2008–9, a rate that was half that of their older counterparts [1]. Similar patterns were seen for general counsellors.

### How can we encourage young people into treatment?

In 2015, 73 %, of Australia’s population were Internet users [14], with highest rates of access reported among young people 93 %, [15]. The internet has become an important source of health information for many people, with evidence indicating that 71 % of young people aged 18–29 search for health-related information online [16]. After e-mail and using search engines, searching for health information is the most popular online activity for adults [17].

The increased availability and use of internet-based programs as a supplement to health care is also a potential solution to well-documented treatment accessibility problems [18], particularly among people with depression and AOD use comorbidity. Treatment can be accessible at times and in locations that suit clients, without the need to schedule appointments or to confront the stigma associated with seeing a therapist. It offers privacy and anonymity, and allows clients to work at their own pace, tailoring the provision of information and strategies. Interactive and multimedia options offer the potential for higher levels of engagement than other self-help modalities [23]. A recent meta-analysis of internet-based interventions for alcohol misuse in adults revealed that they are highly effective in reducing alcohol consumption, and encouraging adherence to low-risk drinking guidelines [19]. Similarly in the depression field, internet-delivered cognitive behaviour therapy has demonstrated effectiveness in reducing depression, particularly when combined with support from a therapist [20]. We have previously demonstrated that, in an adult population, computerised treatment for comorbid depression and alcohol use problems was effective in reducing both depression and alcohol use simultaneously, and produced similar results to a face-to-face integrated intervention delivered by a psychologist [21]. A recent systematic review of treatments for co-occurring depression and substance use in young people highlighted the promise of psychological treatments targeting both issues simultaneously, and the need for more innovative techniques, such as Internet-based technologies, to better engage this group [22].

Social networking is also an increasingly popular online activity for young people, and is most common for Internet users in the younger age groups: 86 % of 18 to 24 year olds performed this activity in 2010–2011 [15]. Facebook is the most widely used of the social networking sites, and in Australia there are currently over 10,000 000 Facebook users, representing 51 % of the Australian population. The majority of these users are young people 12 % for 13–17 years; 24 % for 18 to 24 years; 26 % for 25–34 years, [23]. Results of a 2011 *Sensis®* survey of 803 randomly selected Australians reported that virtually all respondents aged under 30 (93 %) used social networking sites, and the majority accessed these sites every day [24]. Facebook is already frequently used by patients, carers and healthcare professionals to share their experiences with one another [25].

Given the popularity of social networking among young people, there is opportunity for identification and intervention regarding health behaviours particularly in the adolescent and young adult population [26]. Social support, integration, influence and social networks appear to play important roles in both behaviour change and emotional health [27]. Peers are considered more influential than parents in their contribution to adolescent binge drinking through such mechanisms as: modelling; interpersonal persuasion; shaping norms, attitudes, and values; and by providing opportunities and support for problem drinking [28, 29]. As a result, social networking websites have the potential to function as a platform for promoting and establishing (positive and negative) norms of behaviour among young people [30].

## Aims

The internet Treatment for Alcohol and Depression study (iTreAD, http://www.itread.com.au) will conduct the first randomised controlled trial of an Internet-delivered treatment for comorbid depression and binge drinking in young people aged 18–30 years, augmented with social networking support. We will examine the relative impact of:Online monthly self-assessments for 12 months (OSA);OSA + 12-months of access to a 4-week program of web-based intervention for binge drinking and depressed mood (DEpression ALcohol, DEAL);OSA + DEAL + 12-months access to a purpose-built social networking site (Breathing Space).

It is hypothesised that all groups will report reductions in binge drinking frequency and depression over the treatment period, but that this will be greatest for those receiving DEAL. It is also hypothesised that participants allocated to OSA + DEAL + Breathing Space will complete more web-based sessions and therefore report superior reductions in binge drinking frequency and depressive symptoms relative to the other treatment conditions.

### Primary hypothesis

(1) For binge drinking frequency and depression (DASS21) scores at 64 weeks post-baseline, OSA + DEAL + Breathing Space will have a superior impact over the other conditions.

### Secondary hypotheses

(2) Reductions in binge drinking frequency and DASS21 will occur at a faster rate in OSA + DEAL + Breathing Space than the other treatment conditions; and

(3) Participants in OSA + DEAL + Breathing Space will complete a greater number of DEAL sessions and self-assessments, and report greater retention than the other treatment conditions.

## Design

The iTreAD study is a randomised controlled superiority trial, with three parallel groups, and two primary endpoints (changes in depression and alcohol use between baseline and 64-weeks post-baseline assessment). The design is consistent with SPIRIT guidelines for clinical trials [31]. Ethics approval has been obtained from the University of New South Wales Human Research Ethics Committee (Approval #HC13299) as the primary site.

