### Inclusion and exclusion criteria

Inclusion criteria include: (1) aged 18–30 years; (2) current depressive symptoms score at least 5 on the DASS-Depression scale, [32]; (2) binge drinking at least 2 times in the previous month (≥5 standard drinks in the one sitting), as measured by the Alcohol Use Disorders Identification Test – consumption scale AUDIT-c, [33]; and (3) ability to access the Internet. Exclusion criteria are: (1) psychotic symptoms lasting >2 days; (2) non-English speakers; (3) people with organic brain diseases; and (4) serious risk of suicide.

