### Primary endpoint

There are two primary endpoints: (1) depression at 64-weeks post-baseline, and (2) binge drinking frequency at 64-weeks post-baseline.

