### Secondary endpoint

Secondary endpoints are at 64-weeks post-baseline, and include alcohol use, anxiety (DASS-anxiety), service utilisation, and quality of life (using the AQoL). Monthly self-assessment data will be used to track the rate of change in depressed mood and binge drinking frequency between baseline and 12-months post-baseline (the treatment period), to account for any change in symptoms as a function of the baseline assessment session.

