### Sample size and power calculations

Our previous trials indicate approximately 25 % attrition over a 52-week follow-up period [40]. Recruiting 123 participants per group (369 participants across 3 experimental groups) and assuming an attrition rate of 30 %, we anticipate having complete data from 87 participants per group at 64 weeks (*n* = 261).

Our projected sample size at 64 weeks provides sufficient statistical power (at the standard level of 0.80) to detect differences between treatment groups of 0.25 standard deviations or greater, with a type 1 error rate of 2.5 %. Using baseline data from our previous studies with the target population and the DEAL resource [41], this corresponds to a difference between conditions of 1.3 drinks/day, or 9.4/week, and of 2.4 on the DASS21. These differences are towards the lower limits of clinical significance. However, within-condition changes are likely to be substantial. Consistent with our previous research, differences between treatment groups of <0.25SD, provided there are equivalent retention rates and therapeutic alliance ratings, will not be considered clinically significant.

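### The alcohol primary endpoint is worded in two ways, alcohol use is both primary and secondary, and the only alcohol difference given in raw units is not in units of binge drinking frequency

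*Protocol article*

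**What the plan says.** Four parts of the protocol article bear on the alcohol endpoint.

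- **Design:** "two primary endpoints (changes in depression and alcohol use between baseline and 64-weeks post-baseline assessment".
- **Primary hypothesis:** "For binge drinking frequency and depression (DASS21) scores at 64 weeks post-baseline". The **Primary endpoint** section agrees, with "binge drinking frequency at 64-weeks post-baseline" as the second of its two endpoints.
- **Secondary endpoint:** "Secondary endpoints are at 64-weeks post-baseline, and include alcohol use, anxiety (DASS-anxiety), service utilisation, and quality of life". The same section then refers to binge drinking frequency separately, as something tracked by the monthly self-assessments.
- **Sample size and power calculations:** 0.80 power for 0.25 SD at a type 1 error of 2.5%, with 87 participants per group expected at week 64. This is translated into "a difference between conditions of 1.3 drinks/day, or 9.4/week, and of 2.4 on the DASS21".

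The depression outcome is also named loosely. The hypothesis and the sample size section say DASS21, while eligibility uses "current depressive symptoms score at least 5 on the DASS-Depression scale" and DASS-anxiety is a separate secondary endpoint.

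**The concern.** A confirmatory trial has to identify its primary variable before results are seen. As the text stands, an analyst could cite the Design section to call total alcohol use primary, or the Primary endpoint section to call binge frequency primary. The sample size section does not settle the matter, because its alcohol figure is in the units of the Design wording.

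The two variables can give different answers. As an illustration, take two drinking occasions a week at the article's threshold of 5 drinks: 2 × 5 = 10 drinks/week. The same two occasions at twice that amount give 2 × 10 = 20 drinks/week. Binge frequency is identical, yet the weekly quantity differs by 10 drinks, which is more than the 9.4 quoted in the power statement.

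At stake is a post hoc choice between two alcohol outcomes, and a stated alcohol difference that cannot be used to judge a result for binge frequency.

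**Working it through.** **1. The wordings side by side**

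| Section | Alcohol variable | Status |
|---|---|---|
| Design | change in alcohol use | primary |
| Primary hypothesis; Primary endpoint | binge drinking frequency at week 64 | primary |
| Secondary endpoint | alcohol use at week 64 | secondary |
| Sample size | drinks/day, drinks/week | basis of the alcohol difference |

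Alcohol use in the Design section is hard to read as shorthand for binge frequency, because the Secondary endpoint section uses both terms for different things. Change versus value at week 64 matters little, since the analysis model adjusts for the baseline score.

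**2. What the raw-unit figures imply**

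Implied SD = raw difference / 0.25.

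- Daily figure: 1.3 / 0.25 = 5.2 drinks/day.
- Weekly figure: (9.4 / 7) / 0.25 = 1.343 / 0.25 = 5.37 drinks/day.
- DASS21: 2.4 / 0.25 = 9.6 points.

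The daily and weekly figures agree within rounding: 1.3 × 7 = 9.1, and an unrounded value just under 1.35 gives up to 9.45. Neither yields an SD for binge occasions, and the article gives none. On an assumed SD of 3 to 8 binge occasions per month (not from the article), 0.25 SD would be 0.75 to 2.0 occasions per month.

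**3. Type 1 error if both alcohol readings are used**

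Assume the 2.5% is 5% split over two primary endpoints, and take one between-group contrast.

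- Two variables: 2 × 2.5% = 5%.
- Depression plus two alcohol variables: 3 × 2.5% = 7.5%.

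This is an upper bound. Positive correlation between the two alcohol variables lowers the true value.

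**4. Check of the stated power, since any restated difference would carry it forward**

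Inputs: 87 per group (123 × 0.70 = 86.1, close to the stated 87), difference 0.25 SD, type 1 error 0.025, sidedness not stated. The standard error in SD units is √(2/87) = 0.1516, and 0.25 / 0.1516 = 1.649.

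- Two-sided: Φ(1.649 − 2.241) = Φ(−0.592) = 0.277.
- One-sided: Φ(1.649 − 1.960) = Φ(−0.311) = 0.378.

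The stated 0.80 is not reproduced. The difference detectable with 80% power is (2.241 + 0.842) × 0.1516 = 0.467 SD two-sided, or (1.960 + 0.842) × 0.1516 = 0.425 SD one-sided. To reach 0.80 at 0.25 SD, adjustment would have to cut the variance to (0.25 / 0.467)² = 0.29 of its raw value two-sided. That is a baseline correlation of about 0.85 (about 0.81 one-sided), and the article states no such correlation.

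On the same assumed SD of 3 to 8 occasions per month, 0.467 SD is about 1.4 to 3.7 occasions per month.

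**The case against.** The strongest reply is that the intended endpoint is clear. The section headed Primary endpoint names binge drinking frequency, and so do the aims, the primary and secondary hypotheses and the monthly tracking. The outlier is one parenthesis in the Design section. This stands as to intent, and it is why the fix runs in that direction. It does not remove the conflict, because the sample size section supports the outlier.

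A reader might infer that binge frequency has no power figure at all. That is too strong. Power is stated in SD units and could nominally apply to any continuous outcome, and the DASS21 half does refer to the depression primary. The criticism applies only to the alcohol translation.

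A reader might also infer that the DASS21 total competes with the depression subscale as primary, giving four candidate variables and a 10% bound. The documents do not support this. No section makes the total primary, the Primary endpoint section says depression, anxiety is listed separately, and the Discussion reports that a full-scale eligibility criterion was dropped in favour of the depression scale. Nor is the 2.5% level made meaningless; it is weakened if both alcohol readings are used.

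Finally, an article condenses a fuller plan, so instrument and recall window may be fixed elsewhere and are not raised here. The finding concerns contradictory statements, and the Discussion says that the plan reported in the article is the one to be carried out.

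**Conclusion.** The point holds for alcohol. Two alcohol variables can each be called primary by citing the article, alcohol use is listed as both primary and secondary, and the stated alcohol difference is not in the unit of the endpoint named under Primary endpoint. If both variables were tested alongside depression, the error bound for one contrast would rise from 5% to at most 7.5%. That figure assumes that the 2.5% is a per-endpoint share of 5% and that either alcohol result could be claimed.

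The loose DASS21 naming is a minor matter of clarity.

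Separately, 0.80 power at 0.25 SD with 87 per group does not follow from the stated inputs. Without variance reduction from baseline adjustment it is about 0.28 two-sided or 0.38 one-sided.

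**What to change.** Before outcomes are compared by allocated group:

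1. Change the Design section to binge drinking frequency at week 64, matching the Primary hypothesis and Primary endpoint sections.
2. Keep total alcohol consumption as a secondary endpoint only.
3. In the sample size section, either restate the alcohol difference in binge occasions, using an SD from the prior data if one is available, or label the drinks/day figure as referring to the secondary outcome.
4. Recompute any restated detectable difference from the stated inputs, giving the sidedness and any baseline correlation relied on. Do not simply convert 0.25 SD into new units.
5. Write DASS21 depression subscale in the Primary hypothesis and sample size sections, if that is the score intended.

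The cost is a few wording changes, one SD to find, and a short recalculation. Recruitment and data collection need not change.

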### Study setting

Participants will be sought across Australia, via online recruitment strategies (e.g. Facebook, Twitter, Google advertisements, other social media and online forums) and traditional methods (e.g. University campuses, general practitioner surgeries, health service settings, event location promotion). Screening, assessment, treatment and follow-up phases will be conducted in the community, via the Internet, at a time and location convenient to the participants.

### Inclusion and exclusion criteria

Inclusion criteria include: (1) aged 18–30 years; (2) current depressive symptoms score at least 5 on the DASS-Depression scale, [32]; (2) binge drinking at least 2 times in the previous month (≥5 standard drinks in the one sitting), as measured by the Alcohol Use Disorders Identification Test – consumption scale AUDIT-c, [33]; and (3) ability to access the Internet. Exclusion criteria are: (1) psychotic symptoms lasting >2 days; (2) non-English speakers; (3) people with organic brain diseases; and (4) serious risk of suicide.

